### Definitions

Table 2 below shows the definitions of AEs that will be used in the study.

**Table 2. AE definitions**

| **Term** | **Definition** |
| --- | --- |
| Adverse Event (AE) | Any untoward medical occurrence in a participant to whom an IMP has been administered including occurrences that are not necessarily caused by or related to that product. |
| Adverse Reaction (AR) | Any untoward and unintended response to an IMP related to any dose administered. |
| Unexpected Adverse Reaction (UAR) | An adverse reaction, the nature or severity of which is not consistent with the information about the medicinal product in question set out in the SPC for that product, participant information leaflet, IB or protocol. |
| Serious Adverse Event (SAE) or Serious Adverse Reaction (SAR) or Suspected Unexpected Serious Adverse Reaction (SUSAR) ^***^ | Respectively any adverse event, adverse reaction or unexpected adverse reaction that:   - Results in death - Is life-threatening^*^ - Requires hospitalisation or prolongation of existing hospitalisation^**^ - Results in persistent or significant disability or incapacity - Consists of a congenital anomaly or birth defect |

^*^The term life-threatening in the definition of a serious event refers to an event in which the participant is at risk of death at the time of the event; it does not refer to an event that hypothetically might cause death if it were more severe, for example, a silent myocardial infarction.

^**^Hospitalisation is defined as an inpatient admission, regardless of length of stay, even if the hospitalisation is a precautionary measure for continued observation. Hospitalisations for a pre-existing condition, that has not worsened or for an elective procedure do not constitute an SAE.

^***^ Medical judgement should be exercised in deciding whether an AE or AR is serious in other situations. The following should also be considered serious: important AEs or ARs that are not immediately life-threatening or do not result in death or hospitalisation but may jeopardise the participant or may require intervention to prevent one or the other outcomes listed in the definition above.

#### Adverse events

AEs include:

- An exacerbation of a pre-existing illness
- An increase in frequency or intensity of a pre-existing episodic event or condition
- A condition (even though it may have been present prior to the start of the trial) detected after trial medication administration
- Continuous persistent disease or a symptom present at baseline that worsens following administration of the study treatment

#### Exempted adverse events

AEs do not include:

- Medical or surgical procedures; the condition that leads to the procedure is the adverse event
- Pre-existing disease or a condition present before treatment (i.e. a disorder present at the baseline study visit and noted on the baseline medical history/physical examination form/medical notes) that does not worsen
- Hospitalisations where no untoward or unintended response has occurred, e.g., elective cosmetic surgery, social admissions
- Overdose of medication without signs or symptoms

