#### Physical body measurements (baseline, three and six months)

Physical body measurements will include height and weight which will be measured by trained personnel according to the WHO protocols.^57^ These will be used to determine the body mass index. Physical body measurements of the trial participants will not be measured if the recruitment and assessments are conducted remotely, or the intervention is done delivered remotely.

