**Table 1. Baseline and follow-up measurement**

| **Measurement** | **Baseline** | **1 month**  **(Follow-up 1)** | **3 months**  **(Follow-up 2)** | **6 months**  **(Follow-up 3)** |
| --- | --- | --- | --- | --- |
| Demographic data | X |  |  |  |
| Preference for mode of intervention delivery | X |  |  |  |
| Carers/ family members’ involvement | X |  |  |  |
| Details of psychiatric medication | X | X | X | X |
| Smoking status | X | X | X | X |
| Nicotine dependence and urge to smoke | X | X | X | X |
| Quitting smoking intentions, motivations and behaviours | X | X | X | X |
| Mediators of smoking cessation | X |  | X | X |
| Health-related quality of life | X |  | X | X |
| Mental and physical health | X |  | X | X |
| Health services use | X |  | X | X |
| Physical body measurements (height; weight) | X |  | X | X |
| Smoking cessation pharmacotherapy adherence |  | X | X | X |
| Process evaluation questionnaire and interviews |  |  | X |  |

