Pharmacological support: Bupropion and nicotine replacement therapies are generally safe medicines, and have very few side effects. For bupropion, these include nausea, stomach ache, dryness of mouth, sleeplessness, mood changes, appetite changes and headache. We will seek advice from the participant’s mental health care team on whether they can take bupropion before we prescribe this for them. Nicotine gum gives small amounts of nicotine through a gum; and the patches will deliver it through the skin. While the participant will continue to get some nicotine in their system, they will not be exposed to any of the other harmful chemicals that are found in tobacco. Some of the side effects from nicotine gum are mouth or throat sores, bad aftertaste, problems with existing dental work, nausea, jaw pain and racing heartbeat. Some of the side effects of nicotine patches are skin irritation, itching, dizziness, headache, racing heartbeat and nausea. We will advise participants about these potential side effects, and to contact the study team as soon as possible if they suffer from any side effects (serious or otherwise), for us to advise them on what to do. If the side effect(s) are serious enough and the participant feels they need immediate medical attention, they will be informed that they should seek medical help in such circumstances and inform the medical team about their participation in the study and the medicines they are taking as part of the study, and also other medicines that they might be taking.

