### Adverse event monitoring

AEs will be assessed at each counselling session and at the face-to-face follow-up visits, and their potential association with study interventions or procedures ascertained. The researcher conducting the counselling session or follow-up visit assessments will record all directly observed AEs and all AEs reported by the study participant. An adverse events review checklist will be developed to be used at each visit / session to explicitly prompt for symptoms relating to possible nicotine replacement therapy or bupropion related toxicities. This way we will be able to address any AEs or concerns that the participants might have.

In the context of this study, it is very unlikely that any AEs would be related to the behavioural support within the IMPACT 4S intervention nor the BA as they are educational and motivational intervention and that are not harmful. The research procedures are also very low risk. Nevertheless, there is a potential for AEs due to the pharmacotherapies (nicotine replacement therapy or bupropion). AEs will be reported on the AE form. Serious adverse events will be defined according to ICH GCP, and will be reported to the respective country coordinating centres according to the agreed timelines.

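### Adverse events are judged against baseline, but 12 of the 15 listed drug side effects have no prompted baseline record, and the baseline form cited for the exemption is not in the protocol's schedule

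*Protocol*

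**What the plan says.** Section 10.3 has two lists that work together. Under Adverse events, one item counts "Continuous persistent disease or a symptom present at baseline that worsens following administration of the study treatment". Another counts an increase in the frequency or intensity of a pre-existing episodic condition. The third item counts a condition detected after trial medication even where it may have existed before the trial. Under Exempted adverse events, a pre-existing condition that does not worsen is left out, provided it is "a disorder present at the baseline study visit and noted on the baseline medical history/physical examination form/medical notes".

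On timing, section 10.2 states that "AEs will be assessed at each counselling session and at the face-to-face follow-up visits". It adds: "An adverse events review checklist will be developed to be used at each visit / session to explicitly prompt for symptoms". Those symptoms are the possible toxicities of bupropion and nicotine replacement. The baseline visit is not named.

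The side effects are set out in section 10.1. For bupropion, "these include nausea, stomach ache, dryness of mouth, sleeplessness, mood changes, appetite changes and headache"; separate lists follow for nicotine gum and nicotine patches.

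The baseline measures in section 5.15 and Table 1 include the Mood and Physical Symptoms Scale (MPSS), PHQ-9, GAD-7, SF-12, psychiatric medication, height and weight. None is a medical history or physical examination form. Even height and weight lapse in remote work: "Physical body measurements of the trial participants will not be measured if the recruitment and assessments are conducted remotely".

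**The concern.** Both lists in section 10.3 need to know whether a symptom was present at baseline and how bad it was. If nobody asks at baseline, a prompted checklist used during treatment will also pick up long-standing symptoms. Whether such a symptom is then counted or exempted depends on whether someone happened to write it down beforehand.

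The resulting counts are used. Adverse event reports can trigger protocol review and stopping under section 10.8, and the data monitoring committee sees accumulating data under section 12.3. The trial is also meant to show whether the drug component is acceptable enough to carry into a definitive trial. Tolerability rates are not themselves among the listed primary or secondary outcomes, so what is at stake is how far the safety counts can be interpreted, not a headline result.

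**Working it through.** The protocol gives no figure to reproduce here. The check is a count and a comparison of sections.

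**Step 1. Count the distinct side effects in section 10.1.** Bupropion has 7, gum 6 and patch 6, so 7 + 6 + 6 = 19 entries. Nausea is on all three lists (2 repeats), headache on two (1 repeat) and racing heartbeat on two (1 repeat). Distinct symptoms: 19 − 4 = 15.

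**Step 2. Match them to prompted baseline measures in section 5.15.** As the protocol describes it, the MPSS covers anxiety, depression, irritability, restlessness, hunger, concentration and sleep.

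| Prompted at baseline? | Symptoms | Number |
| --- | --- | --- |
| Yes, through the MPSS | Sleeplessness, mood change, appetite change | 3 |
| No measure named | Headache, dry mouth, stomach ache, nausea, dizziness, racing heartbeat, itching, skin irritation, jaw pain, mouth or throat sores, aftertaste, dental problems | 12 |

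3 + 12 = 15. By product, 3 of 7 bupropion symptoms are covered, 0 of 6 for gum and 0 of 6 for patch. PHQ-9 and GAD-7 add depression and anxiety, which the mood row already covers. SF-12 is described only as two component scores.

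**Step 3. Look for the form that the exemption cites.** Eligibility assessment (section 5.6) records age, gender, diagnosis, smoking status, eligibility criteria and screening time. Sections 5.15 and 5.16, with Table 1, hold the items listed above. None of these contains a history or examination form. Of the sources named in the exemption, only the medical notes can be found in the plan.

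**Step 4. Follow one symptom through the rules.** Take a mild dry mouth that predates the trial and does not change.

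- If it is in the medical notes, it is exempt.
- If it is not in the notes and is first reported when the checklist prompts for it after medication, the exemption fails for want of a record. The third item under Adverse events then makes it an adverse event.
- If it is in old notes but the trial team first meets it during treatment, both rules can be argued, because the third item does not say by whom the condition must be detected.

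The symptom is the same in all three cases; only the paperwork differs. The second case shows the direction of the likely error: an undocumented old symptom is counted.

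**The case against.** The strongest reply is that the gap is narrower than it looks.

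- **Medical notes are an accepted source.** Participants are outpatients of the two institutions and are judged stable by their clinical team, so notes will exist. A reader might infer that the exemption hangs entirely on a missing form; it does not. What remains is that nothing in the plan prompts anyone to enter minor physical symptoms in those notes.
- **The checklist is for each visit or session.** A reader might infer that it is used only after treatment starts. The text does not say so: an early counselling session could precede the first dose, and bupropion needs a prior suitability assessment. But the text does not require a pre-treatment use either. Nor is the suitability assessment described as recording symptoms, and section 5.1 ties it to bupropion only.
- **Table 1 is not exhaustive.** It has no adverse event row at any time point and omits the alcohol and substance screening tools named in section 11. This is fair, so the point rests on sections 5.6, 5.15 and 10.2 as well as the table. The adverse event operating procedure, which is not shown, may say more.
- **The control arm gives some background rate.** Both arms attend follow-up, where adverse events are assessed at face-to-face visits. That helps in part. However, Arm 1 has one session against up to 15 in Arm 2, and Table 2 defines an adverse event only in people given an investigational product.
- **Serious events are unaffected.** Identification, causality and notification of serious events do not rest on a baseline symptom checklist. This stands.

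**Conclusion.** The point holds as a gap in the protocol that is cheap to close. For 12 of 15 listed side effects, separating a new symptom from a pre-existing one depends on unprompted medical notes, and the exemption cites a form that the schedule does not contain. The count takes the MPSS content as the protocol describes it and treats symptoms repeated across products as one.

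The likely consequence is over-counting of old symptoms as adverse events. A reader might go further and conclude that new harms cannot be told from old symptoms at all, or that the error could run equally in either direction. The documents do not support this: sleep, mood and appetite have repeated baseline measures, and the third item under Adverse events pushes undocumented old symptoms into the count.

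Nor do the documents support a numerical size. They give no background prevalence for any symptom and no information on how symptoms cluster. The intervention arm of 172/2 = 86 is only an upper limit on the number exposed to the drugs there, because the drugs are offered and participants choose them.

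**What to change.** 1. Give the same symptom checklist once at baseline, before allocation, in both arms, by telephone where recruitment is remote. Record presence, severity and frequency.
2. Add a checklist row to Table 1, marked at baseline and at the later points where it is used.
3. Under Exempted adverse events, replace the history and examination form with this baseline checklist plus medical notes.
4. Reconcile the third item under Adverse events with the exemption, so that a symptom recorded at baseline and unchanged falls clearly on one side.
5. Keep the existing rule that an increase in frequency or intensity is an adverse event. A rule based only on a higher severity grade would lose, for example, headaches that become more frequent within the same grade.

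The checklist is already to be developed, so the cost is a few extra minutes at each baseline interview, one table row and short edits to section 10.3. No extra staff or clinical procedure is needed.

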Participants in this arm will also be offered pharmacological support to aid smoking cessation (nicotine replacement therapy or bupropion either separately or ideally in combination). Pharmacotherapies will be provided for a minimum period of three months. Participants who opt to take bupropion will be referred to their medical doctor for assessing suitability of prescribing bupropion. Participants will be offered sustained-release bupropion, 150 mg/d for the first week and 300 mg/d thereafter. The pharmacological support will be provided for free within the trial. The participants will be scheduled for prescribed medication collection during their face-to-face sessions. In case of changes in mobility restrictions as complying to the local government guideline for managing the upcoming Covid-19 pandemic situation, all scheduled prescribed medication shall be dispatched or personally delivered to the participants’ residential address by post or by research assistants, respectively. Medications for one month will be handed over to them personally by the research staff. An excel sheet log will be maintained for the dispensation, consumption, replenishing and monitoring of Bupropion/Nicotine gums for all the participants who choose pharmacotherapy. The excel sheet log will be filled for medication related details by the research assistants delivering the 4S intervention to the participants and will be centrally managed by the trial manager. The trial manager and the research assistant will monitor the excel sheet log daily to verify if patients would be close to finishing their one-month’s stock of Bupropion/Nicotine gums and need replenishment of a fresh stock. Patient participants who are close to finishing their medications will be given a telephone call one week in advance and asked to visit the NIMHANS campus again to collect the smoking cessation medication for another month; in case, they cannot come to collect the medications, the medications will be personally delivered to the patients. The medications will be provided for a period of three months in total. If there is requirement of bupropion/nicotine gums beyond three months, they will be referred to the treating clinical unit. The patients will be reimbursed the travel costs and compensated for the time they spent in procuring the medication from NIMHANS. The patients will be educated about the correct dosage and method of use, side effects of bupropion/nicotine gums along with an information leaflet on the medications and will be provided contact details to report side effects and for advice. A referral to emergency services will be facilitated in case of a serious adverse event. The participants will be informed to keep the medications in their safe custody and out of reach of children. bupropion/nicotine gums are medications that are routinely prescribed for smoking cessation, including for persons with severe mental illness. Suicide risk assessment will be carried out during the sessions in the intervention arm. Consent to contact family members in case the patient is not reachable on telephone will be sought to mitigate any risks associated with overdose. In case of overdose, a referral to the nearest emergency services will be facilitated. The adherence to medications will be documented in the counsellor’s record book in each session.

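### Symptom-free overdose of trial medication is excluded from adverse events, so a risk the protocol itself names has no stated safety-reporting route

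*Protocol*

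**What the plan says.** **Exemption.** Under Exempted adverse events (section 10.3), the protocol removes "Overdose of medication without signs or symptoms" from the definition of an AE. The line does not distinguish intentional from accidental overdose, trial drug from other drugs, or admitted from non-admitted participants. The same list also removes hospital admissions in which nothing untoward or unintended happened, with elective cosmetic surgery and social admissions as examples.

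**Overdose as a trial risk.** Section 5.1, Arm 2, provides that "Medications for one month will be handed over to them personally by the research staff" and that suicide risk is assessed in the intervention sessions. It adds: "Consent to contact family members in case the patient is not reachable on telephone will be sought to mitigate any risks associated with overdose". It then states: "In case of overdose, a referral to the nearest emergency services will be facilitated". None of this depends on symptoms being present.

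**Seriousness.** Table 2 defines the serious categories as "Respectively any adverse event, adverse reaction or unexpected adverse reaction that" meets one of the listed criteria, hospitalisation among them. A footnote reads: "Hospitalisation is defined as an inpatient admission, regardless of length of stay, even if the hospitalisation is a precautionary measure for continued observation". A further footnote extends seriousness, by medical judgement, to important AEs or ARs that "may jeopardise the participant or may require intervention to prevent one or the other outcomes listed in the definition above".

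**Reporting.** Sections 10.4 and 10.5 send non-serious AEs and ARs to the AE form, and serious ones to the SAE/SUSAR form with 24-hour notice. No separate overdose report is described.

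**The concern.** The protocol supplies bupropion and nicotine replacement to outpatients with severe mental illness and takes precautions against overdose. It then writes the symptom-free overdose out of the only safety-reporting system it describes. An intentional overdose discovered before symptoms develop is informative about whether this way of supplying medication is safe to carry into a definitive trial. What makes it informative is the act and the access to stock, not whether symptoms followed.

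Two things are at stake. First, section 10.8 lets AE reports prompt a review of the protocol or a stop, and an event that is by definition not an AE does not enter that process. Second, with two institutions in two countries, an unclear boundary for admitted cases invites different reporting of the same event, so safety counts would not be comparable between sites.

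**Working it through.** No figure in the plan is at issue, so the check is to trace what the text requires for each kind of overdose of trial medication.

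1. **Overdose with signs or symptoms.** The exemption does not apply. The event is an AE, goes on the AE form, and becomes an SAE if a Table 2 criterion is met. There is no gap here.

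2. **No signs or symptoms, not admitted.** Section 5.1 has an emergency referral facilitated. Section 10.3 says the event is not an AE. Section 10.4 asks for an AE form only for AEs and ARs, so no form is required.

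3. **No signs or symptoms, admitted for observation.** The Table 2 footnote counts an admission as hospitalisation "even if the hospitalisation is a precautionary measure for continued observation". But Table 2 applies its criteria only to something already classed as an AE, AR or UAR, and section 10.4 likewise starts the seriousness assessment from an AE or AR. Section 10.3 has removed the overdose from that class. Its second exemption, for admissions without an untoward response, might remove the admission too, although its examples are of a different kind. Read strictly, no SAE form is due. A site that starts from the footnote would file one within 24 hours.

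4. **No signs or symptoms, but the overdose reflects psychiatric worsening.** The AE list in section 10.3 includes exacerbation of an existing illness. A site could report that worsening as an AE, and as an SAE if it led to admission. The suicidality text in section 5.19 advises emergency admission at medium or high risk but does not ask for an AE or SAE form. Reporting then depends on a site choosing this route although the overdose itself is expressly exempt.

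**Other records.** The dispensing log and the counsellor's adherence record (section 5.1) may reveal an overdose, but neither is a safety report. The AE checklist in section 10.2 prompts for symptoms of drug toxicity, so it is not designed to pick up an overdose without them.

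**Numbers exposed.** With 172 participants allocated 1:1, 172/2 = 86 are in the arm offered medication. At three one-month supplies each, on the three-month total given in section 5.1, that is at most 86 × 3 = 258 handovers. Section 5.1 refers to participants who choose pharmacotherapy and has a doctor assess suitability for bupropion, so actual numbers may be lower. One event would be 1/86 = 1.2% of the full arm. This only gives scale, since the protocol states no expected overdose rate and no safety threshold.

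**The case against.** The strongest objection is that Table 2 and section 10.3 do not contradict each other. A reader might infer that a symptom-free overdose admitted for observation is an SAE under Table 2 and at the same time not an AE. The documents do not support that. Seriousness is a property of an event already classed as an AE or AR, so a precautionary admission is not serious in its own right. This stands, and no strict contradiction should be claimed. It does not remove the concern, because on that coherent reading the event goes unreported even when the participant is admitted.

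Further objections:

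- **Referral is clinical management and can coexist with a narrower AE definition.** True. The referral sentence shows that the protocol regards overdose as important. It does not by itself define an AE.
- **The event could still come to light.** A reader might infer that it can never reach the DMEC or the ethics committees. That is too absolute. Psychiatric worsening may be reported (section 10.3), urgent safety measures must be notified to the York team (section 10.7), and the DMEC sees accumulating data (section 12.3). What stands is that no route is stated for the overdose itself.
- **The AE/SAE reporting SOP may cover it.** It is not available here. Section 10.4 assigns it reporting details and the expected toxicities, and nothing says that it overrides the protocol's definition of an AE.
- **Missing one event would not demonstrably change a safety conclusion.** This stands. There is no threshold against which to judge it, and safety is not among the listed primary or secondary outcomes.

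**Conclusion.** The point holds as a reporting gap with an unclear boundary. A rule written into section 10.3 takes symptom-free overdose of trial medication, including intentional overdose, out of AE reporting, although section 5.1 names overdose as a risk and provides for emergency referral. Such an event has no stated route to the AE form, the SAE form or the AE-based review in section 10.8, unless a site reports the underlying psychiatric worsening. For admitted cases the text can be applied in two ways.

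The gap is confined to overdoses without signs or symptoms; symptomatic ones remain reportable. It could concern at most 86 participants, and the number of events it would hide cannot be estimated from the documents. The conclusion assumes that the SOP does not already require such events to be reported. It takes no position on how an overdose should be managed clinically.

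**What to change.** Reconcile section 5.1 (Arm 2), Table 2 and the exemptions in section 10.3, for reporting purposes only:

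- Remove or amend the overdose line in section 10.3, so that every known or suspected overdose of trial medication, with or without symptoms, is recorded on the AE form and marked intentional or accidental.
- State that the event is notified within 24 hours on the SAE/SUSAR form where a Table 2 criterion is met. Make clear that the exemption for admissions without an untoward response does not cover an admission for observation after an overdose.
- Align the AE/SAE reporting SOP with this text.

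Extending the requirement to overdoses of participants' psychiatric medication would go beyond the defect shown here and is for the sponsor to decide. The cost is a change of a line or two in section 10.3, a matching SOP edit and probably a few additional AE forms. Clinical handling, sample size and analysis are unaffected.
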